#### Secondary Outcomes

⁃ Contrast in participation between the 2 experimental arms and between women that received a questionnaire or not.⁃ Screen test positivity rates (presence of high-risk HPV and distribution by HPV type and/or of abnormal cytology) in the respective arms and contrasts between arms.⁃ Adherence to follow-up of screen-positive women and contrasts between arms.⁃ Impact of covariates on the participation and adherence to follow-up (age, reimbursement status, geographical area).⁃ The obstacles and levers emerging from the speech of the women and health professionals participating in the research will be analysed on the basis of a thematic analysis [21] integrating a specific focus on the indicators identified in previous studies (e.g., lack of time, discomfort with regard to the location or bad experience encountered during another type of examination, etc.). This study will be doubled by a categorical analysis based on Linguistic Inquiry and Word count which allows, among other things, to automatically categorise positive or negative emotions related to themes for example associated with the disease or beliefs [22].

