### Outcomes

#### Primary Outcomes

Participation rates (number of responding/number of invited) in each arm, difference and ratios of participation rates between the control and the two intervention arms.

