### Statistical Methods

The Unit of Cancer Epidemiology (Sciensano, Brussels, Belgium) will perform the statistical analyses of a pseudo-anonymised data file containing records of participating women.

Contrasts in response in women included in the self-sampling arms versus the control arm will be evaluated as relative participation (proportion participating in one arm/proportion participating in another arm) and participation differences (proportion participating in one arm - proportion participating in another arm). A positive response is defined as a woman who has received a screening test: a cervical smear (in the control arm) and a vaginal or urine self-sampling (experimental arm) within 6 months after the offered intervention. The cumulative response rate over time (total number of responses observed by time of observation) will be assessed graphically using Kaplan-Meier curves. Reaching a plateau will indicate that the “invitation effect” is ending and this information will help to define the observation period required to observe the effect of an intervention in the future. Inter-arm contrasts in cumulative participation will be evaluated by Cox’ proportional hazard regression.

Two types of analysis will be performed: per protocol analysis where only responses foreseen in the respective arm will be considered, whereas in the intention to treat analysis also women that are screened not according to the foreseen intervention will be considered as well (also those performed on samples taken by a clinician in the self-sampling arms). The influence of age category and geographical area will be assessed using by Pearson’s *χ*
^2^ statistic and logistic regression.

In addition, knowledge, attitudes, opinions and experiences of participating women, as well as the variation by age, geographical area (including the deprivation index corresponding with the statistical sector where the woman is domiciled) and previous screening history will be assessed in the returned questionnaires.

All statistical analyses will be performed using Stata version 16 (StataCorp LLC, College Station TX, United States). The *p*-value for statistical significance will be defined at ≤0.05.

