### Additional Analyses

#### Laboratory Testing and Gynaecological Follow-Up

The vaginal and urinary self-samples will be analysed at the virology laboratory of the Angers University Hospital using real-time PCR for the search of oncogenic HPV with extended genotyping (BD Onclarity™ HPV test, BD Diagnostics, Burlington, NC). The BD Onclarity™ HPV test provides results for six individual high-risk HPV genotypes (16, 18, 31, 45, 51 and 52), with the remaining eight high-risk genotypes reported in three small groups: (33, 58), (35, 39, 68) and (56, 59, 66). The Onclarity™ assay fulfills requirements for HPV tests in the context of cervical cancer screening [24, 25]. Negative results will be sent to the woman, her GP and the CRCDC. Positive results with oncogenic HPV will be sent to the GP and the CRCDC. The woman will receive a letter urging her to go to her GP to get her result. The CRCDC will follow up with the doctor and the woman if she had not had a smear after 6 months. Reminders will be regularly until the follow-up examination is carried out.

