CapU4 will also monitor the follow-up of screen-positive women in each of the arms through the regional screening centre (CRCDC), with particular attention to the adherence of to the recommendation to have a cervical smear to triage women with an HPV-positive self-sample. The CapU3 study had enabled more than 92% of the women screened to have gynaecological follow-up [20]. The same result is expected in this study.

Strategies that overcome barriers to women’s participation are imperative to improve coverage of cervical screening programmes, but these new strategies also need to be evaluated. The knowledge of obstacles to CC screening will make it possible to optimise the modalities (instructions for use, receipt of results mail) measuring women’s satisfaction. Templates from other countries or regions and suggestions captured from focus-group discussions could help to adapt communication strategies and improve the participation rate of the target population.

This analysis will make it possible to refine the instructions for use and access methods for self-sampling for deployment to all follow-up campaigns in the region and even nationally.

The CapU4 will be completed with an economic analysis where we will assess the incremental cost-effectiveness (extra cost per extra screened woman in the two self-sampling arms versus control arm and in the urinary versus vaginal arms).

Finally, from the qualitative information collected in the in-depth interviews, we will be able to identify the effective strategies for reminders (by simple mail, urinary or vaginal self-sampling kits) for both professionals and the general public.

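### Between-arm contrasts of positivity and follow-up adherence use post-randomisation denominators, so they are not randomised comparisons; a completion outcome per woman invited is missing

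*Protocol article*

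**What the plan says.** The Secondary Outcomes section of the protocol article plans two comparisons that concern what happens after a woman responds:

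- Positivity, which may mean high-risk HPV, an abnormal smear result or both, is to be reported "in the respective arms and contrasts between arms".
- Follow-up after a positive screen is listed as "Adherence to follow-up of screen-positive women and contrasts between arms".

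Only the primary outcome has a stated denominator of invited women: "Participation rates (number of responding/number of invited) in each arm".

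Statistical Methods defines a response as "a cervical smear (in the control arm) and a vaginal or urine self-sampling (experimental arm) within 6 months after the offered intervention". On the test itself, Laboratory Testing and Gynaecological Follow-Up states: "The vaginal and urinary self-samples will be analysed at the virology laboratory of the Angers University Hospital using real-time PCR". For women with a positive self-sample, the same section says "The CRCDC will follow up with the doctor and the woman if she had not had a smear after 6 months", and the Discussion refers to "the recommendation to have a cervical smear to triage women with an HPV-positive self-sample". The follow-up step for a control woman with a positive screen is not written out.

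The per-protocol and intention-to-treat analyses in Statistical Methods settle which responses count as participation. They do not give positivity or adherence a randomised denominator. Nowhere are these two contrasts called descriptive.

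**The concern.** Randomisation makes the three sets of 5,000 invited women comparable. It does not do so for the women who respond, or for the subset who then test positive. The kits are meant to bring in women whom a letter would not reach, so the intervention itself changes who enters these denominators. If the added women are less likely to attend follow-up, the kit arm shows lower adherence even when the arm alters no woman's behaviour.

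For control versus self-sampling there is a second difficulty. The control response is a smear and the kit response is an HPV PCR on a self-sample, so a positive result need not mean the same thing. The monitored step after a positive self-sample is a triage smear. A control responder has already had a sample taken by a clinician, so her next step is probably a different one. Vaginal versus urine shares the assay and the triage step, which leaves only responder selection and specimen type.

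At stake is the reading of the follow-up results. The Discussion foresees wider deployment of self-sampling and stresses follow-up of positive women. A lower adherence figure could count against kits that bring more invited women to a completed episode.

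**Working it through.** **Inputs from the protocol article.** Sample Size gives 5,000 women per arm, control response 12–14%, kit response 3–7 points higher (hence 15–21%), and adherence anywhere from 41% to 92%.

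**Check of the response rates.** The stated 588 to 3,123 per arm is reproduced exactly with a two-sided 5% level, 90% power and continuity correction: 12% versus 19% gives 588, and 14% versus 17% gives 3,123. These rates are therefore the ones the plan rests on.

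**Size of the compared groups.** Control: 5,000 × 0.12 to 0.14 = 600 to 700 responders. Each kit arm: 5,000 × 0.15 to 0.21 = 750 to 1,050.

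**When the two measures disagree.** Let p be response, q positivity and a adherence among positives. Completed follow-up of positives per woman invited is p × q × a. With equal q, the kit arm leads when

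a_kit / a_control > p_control / p_kit.

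| Response, control vs kit | p_control / p_kit |
|---|---|
| 12% vs 15% | 0.80 |
| 14% vs 17% | 0.82 |
| 12% vs 19% | 0.63 |
| 14% vs 21% | 0.67 |

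Between that threshold and 1, adherence among positives favours control and completed follow-up per woman invited favours the kit. If positivity differs, the threshold becomes (p_control × q_control) / (p_kit × q_kit).

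**Can selection alone produce this?** Assumptions:

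- Women who respond to a letter adhere at 92%, and women who respond only to a kit at 41% (the ends of the plan's range).
- The arm changes no woman's adherence.
- Positivity is 8.52% in all. The article does not state this figure. It is what links the stated 1,327 and 4,360 women to the positives needed for a 10-point interval: 113.1 / 1,327 and 371.7 / 4,360 are both about 0.085.

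For 12% versus 19%, kit adherence is (0.12 × 0.92 + 0.07 × 0.41) / 0.19 = 0.1391 / 0.19 = 73%, against 92% in control. Completed follow-up per 5,000 invited is 5,000 × 0.0852 × 0.1391 = 59 with the kit and 5,000 × 0.0852 × 0.12 × 0.92 = 47 in control.

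| Response | Adherence, kit (control 92%) | Completed follow-up per 5,000, kit vs control |
|---|---|---|
| 12% vs 15% | 82% | 52 vs 47 |
| 14% vs 17% | 83% | 60 vs 55 |
| 12% vs 19% | 73% | 59 vs 47 |
| 14% vs 21% | 75% | 67 vs 55 |

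The apparent deficit is 9 to 19 points. With kit-only adherence at 60% it is 6 to 12 points, and at 80% it is 2 to 4 points; in both cases completed follow-up per 5,000 still favours the kit. At 92% it is zero.

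**Precision.** At the same positivity, control has 51 to 60 positives and a kit arm 64 to 89. The 95% half-width for an adherence difference, 1.96 × √[a(1 − a)(1/n_control + 1/n_kit)], is 9 to 10 points at 92% and 16 to 18 points at 41%.

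**The case against.** The best defence is that these are ordinary programme indicators. The Objectives section asks for compliance among women with a positive test, Sample Size plans it for interval width rather than a test, and participation per woman invited is already primary. A careful reader could multiply the reported rates to obtain the yield. All of this stands, and it supports the rates within each arm. It does not cover the between-arm contrasts, which the outcome list plans explicitly and without any caveat.

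The Discussion also reports follow-up above 92% in the earlier uncontrolled urine-kit study and expects the same here. If kit-only responders adhere as well as letter responders, there is no selection bias. This stands as well: the reversal is possible but is not predicted.

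Three further limits hold. The legend of Figure 2 describes follow-up as smear cytology and histology after a possible colposcopy, so adherence is not shown to end at the smear. The difference in follow-up step is inferred, because the control step is not written out. The intention-to-treat analysis counts clinician-taken samples in the kit arms, so those arms may not rest on a single test.

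A reader might go further and infer that the trial is set to report that kits worsen follow-up, or that every arm contrast mixes different tests. The document supports neither. The direction and size depend on adherence not yet observed, and vaginal versus urine uses one assay and one triage step.

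**Conclusion.** The point holds for the between-arm contrasts of positivity and adherence. Their denominators form after randomisation and are expected to differ in size by arm, so the contrasts are not randomised comparisons. For control versus self-sampling the test differs too, and the follow-up step probably does.

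Given equal positivity, the adherence contrast and completed follow-up per woman invited point in opposite directions for adherence ratios between 0.63–0.82 (depending on the response rates) and 1. The 9-to-19-point deficit rests on taking the two ends of the plan's adherence range; it illustrates what selection can do and is not a forecast. The primary participation comparison and the within-arm rates are unaffected.

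**What to change.** 1. Add a secondary outcome with all randomised women as denominator: screening episode completed (negative screen, or positive screen with follow-up recorded) by the existing September 2024 cut-off. Report the difference and the ratio between arms.
2. Keep positivity among women screened and adherence among positives as descriptive figures within each arm. Label any control-versus-kit contrast of them as non-randomised, and state that the tests differ.
3. Show the number of women with a positive screen and follow-up recorded, per woman randomised, as a supporting count only. It depends on how many women each arm's test flags, so it removes the selection problem but not the measurement problem.

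The new outcome will largely follow participation, because most screens are negative. In the 12% versus 19% illustration, control completes 600 × (1 − 0.0852) + 47 = 596 of 5,000 (11.9%) and the kit arm 950 × (1 − 0.0852) + 59 = 928 of 5,000 (18.6%). It should therefore be read beside the within-arm adherence rates.

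The cost is a few lines of text and a little programming. The regional screening centre already collects screening and follow-up results in every arm, and no clinical procedure changes.

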### Sample Size

To demonstrate differences in response rates between the control arm (assumed to vary in the range 12–14%, based on average estimates in a French trial [23] and observations from a meta-analysis [14]) and response rates in the experimental arms (assumed to be 3%–7% higher), a sample size between 588 and 3,123 women per arm would be needed in 1:1:1 randomised trial, accepting a confidence level of 95% and a power of 90%. To estimate the compliance with further follow-up among women with a positive screening test with a 95% confidence interval (CI) width of 10%, assuming compliance rates ranging from 41% to 92% respectively lowest and highest rates observed in a meta-analysis [14], a sample size varying from 1,327 to 4,360 women is needed. By pooling the two experimental arms, it will be possible to obtain more precise (more narrow CIs) estimates of the adherence to further follow-up among women with an HPV-positive result on a self-sample. To conclude enrolment of 3 × 5,000 women will allow sufficient power to demonstrate higher efficacy of the experimental compared to the control arm and to reach sufficient precision to estimate follow-up compliance.

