## Discussion

CapU4 will for the first time compare directly two experimental invitational strategies (including self-sampling of vaginal specimens and collection of first-void urine) with the current procedure including traditional reminder letters with the aim to increase participation in cervical cancer screening. The trial will take place in three rural medically under-served departments, in France, with low screening coverage.

Based on the results of the CapU3 study, we expect that the participation in the self-sampling arms will be between 15% and 20% [20] which should be higher than the response to a routine reminder letter inviting to contact a health professional for the collection of a cervical smear. A recent meta-analysis has shown that strategies including sending self-sampling kits to the women’s home address are more effective than “opt-in” strategies where women have to request a self-sampling kit or routine letters inviting women to have a cervical specimen by a clinician [14]. Another French study also demonstrates that offering a return-mail kit for in-home vaginal self-sampling is more effective and cost-effective than a recall letter in increasing participation in cervical cancer screening [23].

Self-sampling is becoming increasingly important and applicable to supplement organised screening programme. Vaginal self-sampling modalities are recognised in France and recommended for non-participating women since 2019 [10].

Several studies have been set up recently that compares the clinical accuracy of HPV testing on diverse types of self-samples (vaginal, first-void urine) with HPV testing on cervical samples taken by a clinician [16, 37–39].

The areas of the three departments of Sarthe, Mayenne and Vendée are for the most part in the area of medical priority intervention. The healthcare context linked to the COVID-19 pandemic, with three periods of confinement, exacerbates inequalities in access to care with an increase in territorial inequalities due to transport restrictions. The option to collect a self-sample at home may address this accessibility problem. Home-based sample collection should be done in accordance with national recommendations and as part of an organised screening programme that ensures the follow-up of screen-positive women. We will be able to assess accessibility to health services by correlating participation with the density of health services corresponding with the statistical sector.

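### The 1,327 to 4,360 women given for follow-up compliance do not match a 95% CI of full width 10 points, and 5,000 invited per arm does not give that width over the stated 41–92% range

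*Protocol article*

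**What the plan says.** The second calculation in the Sample Size section of the protocol article concerns "compliance with further follow-up among women with a positive screening test". The target is an estimate "with a 95% confidence interval (CI) width of 10"%. The compliance values behind it run from 41% to 92%, the extremes seen in a cited meta-analysis. The result is that "a sample size varying from 1,327 to 4,360 women is needed". The section does not say whether these are invited, screened or screen-positive women.

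It adds that "By pooling the two experimental arms, it will be possible to obtain more precise (more narrow CIs) estimates", and closes by saying that "enrolment of 3 × 5,000 women will allow sufficient power" for the main comparison and will also serve "to reach sufficient precision to estimate follow-up compliance". That conclusion is not limited to the pooled arms or to high compliance.

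Two statements in the Discussion bear on this. For uptake, "we expect that the participation in the self-sampling arms will be between 15% and 20"%. For compliance, the authors cite more than 92% in their earlier urine-kit study and expect the same here.

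**The concern.** Compliance is a proportion among screen-positive women, so its precision depends on how many positives the trial yields. An invited woman contributes only if she takes part and tests positive. With 15–20% uptake, 5,000 invited women give 750–1,000 screened, and the positives are a fraction of those. A requirement of 1,327 to 4,360 women means very different things depending on which of these stages it counts, and setting it beside 5,000 invited women is valid only if it counts invited women.

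Follow-up compliance is a secondary objective, and its contrasts between arms are a listed secondary outcome. A reader who takes the section at its word will expect intervals of ±5 points from each arm, and most will be wider.

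**Working it through.** **Inputs.** From Sample Size: full width 0.10, compliance p = 0.41 to 0.92, required number 4,360 to 1,327, 5,000 invited per arm. From the Discussion: participation 15–20% in the kit arms. Positivity: not given, so treated below as implied or assumed.

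**1. Trying to reproduce the printed figures.** Wald formula, n = 1.96² p(1−p)/h², where h is the half-width.

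- h = 0.05 (full width 10 points): 3.8416 × 0.2419/0.0025 = 371.7, so 372 positives at 41%; 3.8416 × 0.0736/0.0025 = 113.1, so 114 at 92%.
- h = 0.10 (full width 20 points): 92.9, so 93; and 28.3, so 29.

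Neither pair is 4,360 and 1,327. Wilson and Clopper-Pearson intervals do not give them either (about 368 and 118, or 390 and 133, for full width 10 points). The ratio does agree: 4,360/1,327 = 3.286 and 0.2419/0.0736 = 3.287. So the printed pair is the Wald count divided by one constant:

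- h = 0.05: 371.7/4,360 = 0.0853 and 113.1/1,327 = 0.0852
- h = 0.10: 92.9/4,360 = 0.0213 and 28.3/1,327 = 0.0213

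By contrast, the primary-outcome range in the same section reproduces exactly with a continuity-corrected two-proportion formula at 90% power: 14% v 17% gives 3,123 and 12% v 19% gives 588.

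**2. What the constant could be.**

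- *Screen-positive women.* 4,360 positives at 41%, or 1,327 at 92%, would give a width of 2.9 points, not 10. Also, 750–1,000 screened cannot contain 1,327 positives. Ruled out.
- *Invited women, full width 10.* The constant would be participation × positivity, so positivity = 0.0853/0.20 to 0.0853/0.15 = 43–57%. Not credible.
- *Invited women, half-width 10.* Positivity = 0.0213/0.20 to 0.0213/0.15 = 10.7–14.2%. Credible, and 4,360 is then rightly compared with 5,000. The full width is 20 points.
- *Screened women, full width 10.* Positivity = 8.5%. The requirement is then 1,327–4,360 screened, against 750–1,000 per kit arm and 1,500–2,000 pooled.

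**3. Widths achieved.** Width = 2 × 1.96 × √(p(1−p)/m), with m positives. The invited reading gives m = 5,000 × 0.0213 ≈ 107 per arm and 213 pooled. The screened reading gives m = 750 to 1,000 × 0.0853 ≈ 64–85 per arm and 128–171 pooled. The last two rows use an assumed positivity of 10–15% with 15–20% participation.

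| Basis | Positives | Width at 41% (points) | Width at 92% (points) |
|---|---|---|---|
| Invited reading, one kit arm | 107 | 18.7 | 10.3 |
| Invited reading, pooled | 213 | 13.2 | 7.3 |
| Screened reading, one kit arm | 64–85 | 24–21 | 13–12 |
| Screened reading, pooled | 128–171 | 17–15 | 9.4–8.1 |
| Assumed 10–15%, one kit arm | 75–150 | 22–16 | 12–9 |
| Assumed 10–15%, pooled | 150–300 | 16–11 | 9–6 |

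**4. Positivity needed for a full width of 10 points.** At 41%: 372/1,000 to 372/750 = 37–50% per arm, and 372/2,000 to 372/1,500 = 19–25% pooled. At 92%: 11–15% per arm and 5.7–7.6% pooled.

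**5. Compliance from which the pooled kit arms reach 10 points.** The condition is p(1−p) ≤ m × (0.05/1.96)² = m × 0.000651. For m = 213 this is 0.139, so p of about 83% or more. For m = 128–171 it is 0.083–0.111, so p of about 91% down to 87%.

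**The case against.** The strongest defence is that the sample size is sound and only one word is wrong. If ±10 points was meant, 4,360 invited women is a coherent requirement at the low end, 5,000 exceeds it, and each arm achieves about ±9.4 points (18.7/2) at 41%. The Discussion expects compliance of about 92%, where one arm comes within a few tenths of a point of the 10-point width on this reading and the pooled arms meet it easily. The section itself points to pooling for tighter intervals. The participation and positivity inputs are details that a condensed article may leave to the full protocol.

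Much of this stands. The half-width reading is the likelier one, and missing inputs are not in themselves an error. But the section did not size on 92%: it chose 41–92%, and 4,360 belongs to the 41% end. It states a width, not a margin, and pooling does not reach 10 points at that end. Nor can pooling serve the contrasts between arms listed under Secondary Outcomes.

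A reader might go further and infer that the trial yields far too few positives throughout, that intervals will be about 2.4 times as wide as promised, or that more than 20,000 women per arm must be invited. The documents do not support this. Those figures rest on a positivity of 8.5% that is back-solved from the disputed numbers and on the less likely reading, and at about 92% compliance the pooled kit arms meet the target on both readings.

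**Conclusion.** The statement is wrong as written. The stated requirement of 1,327 to 4,360 women does not follow from a full width of 10 points, which needs about 372 and 114 screen-positive women at the two ends of the range. On either credible reading, 5,000 invited per arm misses that width over 41–92%. The pooled kit arms miss it at the lower end and meet it at about 92%, where one arm is borderline (10.3 points) or short (12–13 points).

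Across the two implied rates, achieved widths are about 10–24 points per kit arm and 7–17 pooled. These depend on the Discussion's 15–20% participation and on a positivity rate that the article does not state. Two findings need no outside positivity figure: the printed numbers do not reproduce for the stated width, and if they count screened women, 750–1,000 per kit arm falls below even 1,327. The documents cannot settle which reading the authors used. The error concerns the precision of a secondary estimate; power for the primary outcome is not affected.

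**What to change.** Keep 3 × 5,000 and correct the text of the Sample Size section:

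- State whether 10% is a full or a half width. If half, write ±10 points.
- State whether 1,327–4,360 counts invited or screened women, and give the participation and positivity rates used.
- Replace the general claim of adequate precision for follow-up compliance with the achieved widths, per arm and pooled, at low and high compliance. Calculate them from the authors' own positivity rate, shown as an assumption with a range.
- Limit any claim of a 10-point full width to the pooled kit arms at high compliance: about 83% or more on the invited-women reading, nearer 92% (about 87–91% or more) on the screened-women reading.

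The cost is wording and a less favourable stated precision for a secondary outcome. No extra women are needed.
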